## 3. Results and Discussion

The MS-CHAT trial will test if trained medical students can improve smoking cessation outcomes among hospitalized patients who smoke tobacco. This is a potentially scalable, low-cost model that combines medical student skill development with inpatient smoking cessation counseling. Providing experiential training to medical students has the potential to increase the delivery of smoking cessation counseling when they step into practice, by increasing their comfort with this skill. Furthermore, the skills acquired in MS-CHAT may enable medical students to provide counseling for diet, physical activity, and other behavioral barriers to optimal health [11].

## 4. Conclusions

The findings of this trial will have implications for noncommunicable disease intervention strategies not just in other low- and middle-income countries but potentially also in advanced health care systems tackling some of the same issues.

## Figures and Tables

**Figure 1 fig1:**
[figure not shown]
Location of study sites in India.

**Figure 2 fig2:**
[figure not shown]
Structure of study.

**Table 1 tab1:** Definitions.

7-day quit rate: defined as the patient's self-reported smoking behavior in the last 7 days. Assessed as “Have you refrained from smoking during the past seven days, and not smoked even one puff?”
Continuous abstinence: defined as being abstinent from smoking for at least the prior 90 days. Patients will be asked to specify quit date or number of weeks/months since quitting.
Biochemical testing: breath carbon monoxide < 10 PPM constitutes a verified successful quit attempt.
Previous quit attempt: a 24-hour quit attempt in the past 12 months.

**Table 2 tab2:** Planned secondary outcomes.

Patient outcomes:
(i) Biochemically verified 90-day quit rate, measured 6 months after enrollment. (ii) Number of patients achieving a 50% reduction in the number of cigarettes/bidis smoked in a week, measured at 2 and 6 months after enrollment. (iii) Correlation between verified quit rates at 6 months and FTND scores at enrollment. (iv) Correlation between verified quit rates at 6 months and number of quit attempts, by the study group. (v) Number of patients who report having quit smoking in the last 7 days at 2 and 6 months from enrollment (irrespective of biochemical verification). (vi) Agreement between self-reported 7-day quit rate and biochemically verified 7-day quit rate, measured at 6 months from enrollment. (vii) No. of patients who have refrained from using smokeless tobacco in the last 7 days, measured at 6 months from enrollment. (viii) Per protocol analysis of the 7-day quit outcome, 6 months after enrollment. Patients in the intervention arm who did not receive a hospital counseling session and at least two follow-up phone calls will be excluded.
Medical student outcomes:
(i) Pre-post analysis of medical student knowledge about counseling techniques and pharmacotherapy before, 6 weeks, and 12 months after training. (ii) Correlation between scores on the knowledge survey with patient quit rates. (iii) Qualitative analysis of the effectiveness of the training modules assessed by student survey, administered 6 weeks after training. (iv) Qualitative analysis of student attitudes towards smoking cessation counseling as assessed by a survey, administered 12 months after training. (v) Qualitative analysis of the trial design and implementation as assessed by a survey administered 12 months after training.

**Table 3 tab3:** Planned descriptive outcomes.

Descriptive outcomes: (i) Number of enrolled patients that receive inpatient counseling and at least 3 follow-up calls, calculated at 2 months from enrollment. (ii) Number of patients who use any form of cessation pharmacotherapy within the first 2 months of enrollment. (iii) Number of patients enrolled in the study that are available for follow-up at 6 months from enrollment.

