#### 2.2.1. Trial Design and Participants

This is an open-label, two-armed, parallel-group, block randomized controlled trial with 1 : 1 concealed allocation. Patients are the unit of randomization. Eligibility criteria include age 18-70 years, active admission to the hospital, and current smoking or report having smoked in the last four weeks prior to admission (to account for changes in behavior during illness). Eligible patients are stratified based on the medical school and block randomized into an intervention or control group using a block size of 20. Opaque envelopes developed by the research team are provided to the coordinators to be used for randomization.

Exclusion criteria include patients using only nonsmoked tobacco and those who are daily alcohol users or daily drug users. Patients deemed unable to follow-up, either because of distance from the hospital or because of psychiatric, social, or medical factors, will be excluded. Patients currently participating in another tobacco cessation program are also excluded.

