### 2.5. Sample Size and Statistical Analysis

We calculated the sample size needed for a study with a power of 85%, *α* of .05 to detect a 10% absolute difference in the primary outcome assuming a control quit rate of 20%. This was based on a prior meta-analysis of tobacco cessation interventions among hospitalized smokers [4]. We assumed an attrition rate of 20%. Based on these calculations, a sample size of 830 patients will be required, resulting in 415 patients in the intervention and a similar number of patients in the control group.

The primary outcome will be analyzed by an intention-to-treat approach. Patients lost to follow-up at any time point will be considered as smokers for analysis. A secondary analysis with smoking status at last phone contact will be performed.

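### Per-protocol outcome (viii) drops non-adherent patients from the intervention arm only, so it is expected to favour the intervention by an amount the documents do not determine

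*Protocol article*

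**What the plan says.** Table 2 lists as patient outcome (viii): "Per protocol analysis of the 7-day quit outcome, 6 months after enrollment". The population is then defined: "Patients in the intervention arm who did not receive a hospital counseling session and at least two follow-up phone calls will be excluded". No restriction is given for controls. Under section 2.2.3 they receive usual care, so no student calls exist by which a comparable group of controls could be identified.

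Section 2.5 says of the main comparison: "The primary outcome will be analyzed by an intention-to-treat approach". The next sentence is: "Patients lost to follow-up at any time point will be considered as smokers for analysis". Neither section 2.5 nor Table 2 exempts (viii) from that rule.

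Under section 2.2.2 the post-discharge counselling is delivered by telephone over two months. Under section 2.3 the six-month outcome is obtained by contacting the patient, and those who report quitting are called in for a breath test.

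**The concern.** Receiving the hospital session and two calls happens after randomisation. It depends partly on whether the patient can be reached and is willing to talk. Reachability also affects whether the patient is found at six months, and a patient who is not found counts as a smoker. The rule thus tends to remove patients who would count as smokers through loss from the intervention arm, and leaves their counterparts among the controls. Patients who accept repeated counselling may also be more motivated to quit, and they are compared with unselected controls. Both mechanisms push towards the trial's hypothesis.

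At stake is the reading of one secondary result. A per-protocol estimate is easily taken as the effect of counselling actually received, and here part of it could be selection.

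**Working it through.** **Inputs from section 2.5.** The design has "power of 85%, *α* of .05 to detect a 10% absolute difference in the primary outcome assuming a control quit rate of 20" per cent; "We assumed an attrition rate of 20" per cent; and "a sample size of 830 patients will be required, resulting in 415 patients in the intervention", with the same number of controls. Allocation is 1:1 (section 2.2.1). The significance level is taken as two-sided, since the article does not say.

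**The plan's own figure.** With unpooled variance, n per arm = (1.960 + 1.036)² × (0.20 × 0.80 + 0.30 × 0.70) / 0.10² = 8.978 × 37 = 332.2. Dividing by 0.80 gives 415.25, which agrees with 415 per arm and 830 in total. The pooled formula gives 336, then 420 per arm and 840. The sample size is not in question.

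**Assumptions not in the documents.**
- There is no treatment effect.
- The 20% quit rate applies to all randomised patients with losses counted as smokers. With 20% lost, the rate among those followed is 0.20 / 0.80 = 25%, the same in every subgroup.
- 20% of the intervention arm fails the adherence rule, leaving 415 × 0.80 = 332 patients.
- The lost-equals-smoker rule applies to (viii).

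**Formula.** Let Lₑ be the loss among excluded intervention patients and Lₐ the loss among those retained, with 0.20 Lₑ + 0.80 Lₐ = 0.20. The per-protocol intervention rate is 0.25 × (1 − Lₐ). The control rate stays at 0.25 × 0.80 = 20%. Rejection is the two-sided probability from a pooled two-proportion z-test with 332 against 415 patients.

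| Lₑ | Lₐ | Per-protocol rate | Control rate | Spurious gain | Rejection |
|---|---|---|---|---|---|
| 20% | 20% | 20.0% | 20% | 0 | 5% |
| 30% | 17.5% | 20.6% | 20% | +0.6 points | 5.5% |
| 40% | 15% | 21.25% | 20% | +1.25 points | 7% |
| 60% | 10% | 22.5% | 20% | +2.5 points | 13% |
| 100% | 0% | 25.0% | 20% | +5.0 points | 37% |

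A simulation of 200,000 trials gave the same 13% and 37% for the last two rows. The last row is the upper bound at this exclusion fraction: the excluded are exactly the patients lost. The first row shows when the bias vanishes, namely when missed sessions are unrelated to loss (and to quitting).

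**Other baseline.** If 20% is instead the quit rate among those followed, controls are at 0.20 × 0.80 = 16%. The last two rows become 18% against 16% (+2.0 points, 11%) and 20% against 16% (+4.0 points, 30%). The pattern is the same and somewhat smaller.

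**The case against.** **The link may be weak.** The documents give neither the fraction excluded nor how far it overlaps with loss at six months. The rule speaks of sessions not received, and sessions are delivered by volunteer second-year students, so some omissions will be the student's doing. With a weak link the gain is 0.6 to 1.25 points and rejection stays close to nominal. This stands, and it is why only a range can be given. It does not restore the randomised comparison: the bias is zero only if the excluded patients would do as well as those retained, and nothing in the article supports that.

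**The smoker rule may not apply.** It sits in the paragraph on the primary analysis. If (viii) used only patients followed at six months, the calculation above would give 25% against 25% and no bias from loss. Application to (viii) is the natural reading, because the rule is worded generally and no exception is made, but it is not explicit. Selection on motivation would remain under either reading. It is not quantified here.

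**A stronger reading.** A reader might infer that the analysis will show a benefit when there is none. The documents do not support that. The claim is one of bias in expectation, and even at the upper bound a trial with no effect is non-significant 63% of the time (100 − 37). Nor does the article say that (viii) will be presented as the effect of counselling received. It is one of eight secondary patient outcomes and is labelled per protocol.

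**The replacement has its own bias.** A complier-average estimate treats counselling below the threshold as having no effect. If full adherers gain 10 points and the 30% below threshold gain 5, the intention-to-treat difference is 0.7 × 10 + 0.3 × 5 = 8.5 points, and 8.5 / 0.7 = 12.1 overstates the effect in adherers by 2.1. This stands and must be declared. Under no effect, however, the intention-to-treat difference has expectation zero and the estimate is not pushed towards benefit, unlike (viii).

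**Conclusion.** The concern holds in a limited form. As written, (viii) excludes on a post-randomisation condition in one arm only, and the result is expected to be biased towards the intervention. This is in the article's own definition of the population and does not depend on detail left to an analysis plan.

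On the assumptions listed, the spurious gain lies between about 0.6 points with a weak link and 5 points at the upper bound, against a 10-point design effect. A larger excluded fraction could raise the upper bound. Only this secondary outcome is affected. The primary intention-to-treat analysis and the sample size are not. The change should be made, but nothing in the main conclusion of the trial hangs on it.

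**What to change.** Replace (viii), as the estimate of the effect of counselling received, with a complier-average causal effect:

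- Divide the intention-to-treat difference in quitting by the proportion of the intervention arm meeting the existing adherence definition.
- Use randomisation as the instrument, keep all randomised patients, and give a bootstrap or delta-method confidence interval. Controls have no planned student counselling, so non-adherence can reasonably be treated as one-sided.
- State that the outcome is the biochemically verified one. Table 1 defines the 7-day quit rate by self-report, and (viii) does not say which is meant.
- State the assumption that counselling below the threshold has no effect, and that the estimate overstates the effect in full adherers if partial counselling helps.

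If the one-sided per-protocol comparison is still reported, label it descriptive and subject to selection bias in favour of the intervention, and say how losses are handled in it.

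The cost is analysis wording only. The adherence data are already needed for (viii) and for the first descriptive outcome in Table 3. The price is a wider confidence interval and the assumption above.

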## 1. Introduction

Global Adult Tobacco Survey (GATS) 2016 showed that India had 100 million smokers [1]. Smoking cessation substantially reduces the risk of death associated with smoking, and interventions to quit smoking are both efficacious and cost-effective [2, 3]. Studies have shown that counseling hospitalized patients is effective if started during hospitalization and continued for at least a month after discharge [4]. However, numerous barriers exist to widespread adoption of this practice [5].

Most physicians lack the necessary knowledge and skills to offer effective cessation counseling to their patients [6, 7]. This gap likely starts from medical school [8]. Purely didactic-based teaching may not be sufficient in preparing students for independent practice, particularly if inadequately supplemented with the varied experience of counseling actual patients [9]. Educational interventions have been found to have greater student engagement when they include a component of integrative learning, such as in a real patient encounter [10].

We designed the current study to test the hypothesis that utilizing trained medical students to counsel hospitalized smokers will lead to an increase in patient quit rates, while also improving medical student knowledge and confidence regarding smoking cessation counseling.

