#### 2.2.2. Intervention Group

Participating medical students offer inpatient counseling to patients in the intervention group once during their hospitalization (recommended duration of 15-20 minutes). The medical students then follow-up with their patients and provide telephone counseling (a minimum of three sessions of 15 minutes each, over two months).

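### Table 2 (viii) labels as per protocol a set that admits patients with two follow-up calls, although Section 2.2.2 sets a minimum of three

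*Protocol article*

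**What the plan says.** Three places in the protocol article state how much counseling counts.

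- **Section 2.2.2 (Intervention Group)** describes what students deliver. There is one inpatient session: "Participating medical students offer inpatient counseling to patients in the intervention group once during their hospitalization". Telephone counseling follows, with "a minimum of three sessions of 15 minutes each, over two months".
- **Table 3 (i)**, a descriptive outcome, counts delivery as "Number of enrolled patients that receive inpatient counseling and at least 3 follow-up calls, calculated at 2 months from enrollment".
- **Table 2 (viii)**, a secondary patient outcome, is introduced as "Per protocol analysis of the 7-day quit outcome, 6 months after enrollment". Its inclusion rule is "Patients in the intervention arm who did not receive a hospital counseling session and at least two follow-up phone calls will be excluded".

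For the primary outcome, Section 2.5 states: "The primary outcome will be analyzed by an intention-to-treat approach".

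**The concern.** A reader takes a per-protocol analysis to describe patients who were treated as the protocol lays down. The article lays down at least three telephone sessions and uses three again when it counts delivery, but its per-protocol set asks for two calls. Some patients in that set may therefore have received less than the article's own minimum.

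What is at stake is interpretation. Whether the estimate from (viii) is favourable or null, it could not be attributed to the program described in Section 2.2.2, because the set is defined by a lower amount of counseling. If the mismatch is noticed only at analysis, someone must then choose between a two-call and a three-call set when the outcome data may already be visible.

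**Working it through.** **Thresholds side by side**

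| Place | Inpatient session | Calls | Purpose |
|---|---|---|---|
| Section 2.2.2 | one | at least 3 | what is to be delivered |
| Table 3 (i) | yes | at least 3 | descriptive delivery count |
| Table 2 (viii) | yes | at least 2 | per-protocol analysis set |

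**Classifying an intervention patient who had the inpatient session**

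| Calls received | Meets Section 2.2.2 minimum | Counted in Table 3 (i) | In the Table 2 (viii) set |
|---|---|---|---|
| 0 or 1 | no | no | no |
| exactly 2 | no | no | **yes** |
| 3 or more | yes | yes | yes |

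The rules part company in the middle row only.

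**Does this depend on how the texts are read?**

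1. The exclusion sentence in (viii) could be misread as dropping only patients who lack both components. On that reading, a patient with the session and two calls is still kept, so the middle row does not change.
2. Section 2.2.2 speaks of sessions and (viii) of calls. If these were different things, Section 2.2.2 might not be comparable with (viii). Table 3 (i), however, also speaks of follow-up calls, as (viii) does, and asks for three.

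**Does it touch the sample size?**

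Inputs from Section 2.5 are a 20% control quit rate, a 10-point absolute difference (so 30%), 85% power, alpha 0.05 and 20% attrition. Alpha is taken as two-sided, which the article does not state.

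- Unpooled variance: n = (0.20×0.80 + 0.30×0.70) × (1.960 + 1.036)² / 0.10² = 0.37 × 8.978 / 0.01 = 332.2, so 333 per arm. Then 333/0.80 = 416.25, so 417 per arm and 834 in total. Without rounding up at the first step, 332.2/0.80 is about 415, which is the stated figure per arm.
- Pooled variance: 336 per arm. Then 336/0.80 = 420 per arm and 840 in total.

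Both agree closely with the stated 830. The calculation concerns the primary outcome, which is analysed by intention to treat. No call threshold enters it.

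**How many patients?**

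The article gives no call-completion rate, so the share with exactly two calls is unknown. For scale only, assumed shares of 5%, 10% and 20% of the 415 intervention patients would be 0.05×415 ≈ 21, 0.10×415 ≈ 42 and 0.20×415 = 83. These shares are assumptions and carry no weight in the conclusion.

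**The case against.** The best defence is that the three statements do different jobs: one instructs the students, one counts full delivery, and one defines an analysis set. A prespecified adherence cut-off below full delivery can be legitimate, and this one is stated openly, so an analyst can apply it and a reader can see it. That stands as a defence of having a two-call set. It does not defend calling that set per protocol without a reason when the protocol's minimum is three.

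The defence also disposes of several stronger conclusions that a reader might infer:

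- **That the trial would report incompatible adherence figures.** It would not. Table 3 (i) is the only delivery count, and the sets are nested: every patient with the session and three calls also has the session and two.
- **That (viii) is defective because it gives no time window for the calls.** Section 2.2.2 already places the sessions over two months, and a restated window is detail that the full protocol or analysis plan may hold. The Introduction's remark that counseling is "effective if started during hospitalization and continued for at least a month after discharge" is background from earlier studies. It is not a rule for this set.
- **That the two-call patients dilute the estimate.** The direction is unknown. The exclusion applies to the intervention arm only, so a stricter cut-off would remove more patients on post-randomisation grounds and leave the control arm whole. That could add selection bias.
- **That a large part of the arm is affected.** Any such figure needs an assumed completion rate, an assumed number of call attempts and an assumption about who received the inpatient session. The article supplies none of these.

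**Conclusion.** The mismatch is real and visible in the current text. By the article's own minimum, the per-protocol set admits patients who were not treated per protocol, and the article does not say why. The estimate from (viii) therefore describes patients with the inpatient session and at least two calls, and should not be reported as the effect of the program as specified.

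The severity is minor. This is one secondary analysis, and the primary intention-to-treat result and the sample size do not depend on it. Neither the number of patients affected nor the direction of any effect can be determined from the article. The conclusion assumes that a follow-up call in Tables 2 and 3 is a telephone session in the sense of Section 2.2.2, and that no reason for the two-call cut-off stands in a fuller document that is not shown. Such a reason would justify the cut-off, but the label would still not match Section 2.2.2.

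**What to change.** Reconcile Section 2.2.2, Table 2 (viii) and Table 3 (i) before outcome data are analysed by arm. Which number of calls applies is for the sponsor to decide. There are two ways to do it:

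1. Use one delivery threshold for both the stated intervention minimum and the per-protocol set.
2. Keep the two-call set, rename it as an analysis of patients with partial delivery or better (a minimum-exposure set), and give the reason for the cut-off.

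In either case, tabulate intervention patients by inpatient session (yes or no) and by 0, 1, 2 and 3 or more calls, so that readers can see how many fall between the two thresholds.

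The cost is a wording change and one table from call records that Table 3 (i) already needs. If the set is made stricter, it becomes smaller and less precise. Because only the intervention arm is restricted, it also becomes more selected, and the report should say so. Relabelling avoids that cost, but leaves the trial without an analysis restricted to patients who received the stated minimum.

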## Data Availability

There is no data collection associated with this paper.
